### **11.4 Sample Size Considerations**

#### **Sample Size and Power Estimation:**

##### **11.4.1 Objectives**

The K23 study is intended to provide pilot data to support an R01 application for a larger fully-powered RCT. In a staged model of treatment development [ PA-03-066], a pilot study is where “data are gathered to estimate intervention parameters (e.g., effect size, attrition, rates, response rates) and to perform preliminary power analyses” [NIMH PAR-03-078]. Therefore, the proposed project will estimate treatment parameters for FA and OM modules relative to MBCT to inform future larger-scale trials, not necessarily to determine absolute significance levels. A larger R01 trial will be needed for a definitive test to detect if true differences exist between treatments.

##### **11.4.2 Feasibility limitations – maximum capacity**

Based on a maximum of 9-12 groups of 8-12 participants, our maximum capabilities are about approximately 90-110 (enrolled) participants.

##### **11.4.3 Relevant pilot data:**

For our lab's MBCT trial (n=45), which consisted of a very similar population, intervention and equipment to the proposed study, effect sizes (Cohen's d) for MBCT vs. Waitlist Control) were  
.89 for depression (BDI) (large)  
.72 for decrease in SWS (large)  
.75 for decreased emotional reactivity (i.e. large).

##### **11.4.4 Basic Calculations**

While effect sizes in mood and sleep following mindfulness training are large, the differences between active treatments tend to be small (Wampold et al., 1997). A sample size of 90 (30 per intervention) will be able detect a small effect size ( $d=.33$ , power  $>.80$ ,  $\alpha=.05$ ).

**Method of calculation: G\*power 3.1.3****F tests - ANOVA:** Repeated measures, within-between interaction

**Analysis:** A priori: Compute required sample size  
 $\alpha$  err prob = 0.05  
Power (1- $\beta$  err prob) = 0.80  
Number of groups = 3  
Number of measurements = 2  
Nonsphericity correction  $\epsilon$  = 1

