## 11.2 Objectives and Hypotheses:

The analysis is divided into 3 categories:

Preliminary Analysis includes assessment of delivery and acceptability of treatments, and any group inequalities that may have resulted from treatment randomization, attrition and compliance

Primary Analysis assesses: Effect of treatments on clinical outcome (negative affect/depression) and (secondary analyses) effect of treatment on mechanism of action.

Differences in clinical outcomes between active treatments tend to be small. Thus, given our sample size, we do not predict a significant difference between single-component the standard package in terms of clinical efficacy. However, because single practice interventions are less complex and easier to implement, non-inferiority to standard treatment has significant clinical meaning.

The largest group differences are hypothesized in terms of mechanism of action. Specifically, we predict: Attention training (FA) will differentially improve attention (FA>MBCT>OM)  
Acceptance training (OM) will differentially improve emotional non-reactivity (OM>MBCT>FA).

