**Output**

**Total sample size = 90**  
**Effect size d = .335**

### 11.4.5 Additional Sample size considerations +modifications

#### 11.4.5.1 Attrition

Based on pilot studies, we estimated 15% attrition rate (Shahar et al., in press) so that we need to enroll a total of 105 subjects (35 per group) in order to have 90 completers.

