### 11.4.6 Multiple comparisons

Using the current sample size of 90, we will still be able to detect a small sample size ( $d=.43$  while correcting for up to 10 multiple comparisons with a Bonferroni correction ( $p=.05/10 = .005$ ).

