### 11.4.7 Minimum Sample Size

It is possible that recruitment will be slower and attrition higher than anticipated. Below are the detectable effect sizes with alternative sample sizes (at .80 power,  $p<.05$ , no adjustments)

- N=75 (25 per group ) d=.37 (small)
- N=45 (15 per group) d=.48 (small, approaching medium)

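### The detectable effects of .33/.335, .43, .37 and .48 in 11.4 are not Cohen's d; 30 per arm does not give 80% power for a small difference between arms

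*Protocol*

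**What the plan says.** Section 11.4.4 says that "A sample size of 90 (30 per intervention) will be able detect a small effect size", quantified as d = .33 with power above .80 at alpha .05. The method is G*Power's F test "Repeated measures, within-between interaction", with "Number of groups = 3" and "Number of measurements = 2". The input list gives no correlation between the repeated measures. The output reads "Effect size d = .335" for a total of 90.

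Section 11.4.6 says that after a Bonferroni correction to .005 "we will still be able to detect a small sample size" (an effect size is meant), with d = .43. Section 11.4.7 gives d = .37 for N = 75 and "N=45 (15 per group) d=.48 (small, approaching medium").

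Section 11.4.3 reports Cohen's d of .89 for MBCT against waitlist in the pilot trial. Section 11.2 expects differences between active treatments to be small, predicts no significant difference in clinical efficacy, and adds that "non-inferiority to standard treatment has significant clinical meaning". It sets no margin. Sections 11.1 and 11.4.1 describe the aim as estimating parameters for a later trial.

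**The concern.** The named procedure works in Cohen's f, but the protocol reports d. Doubling f gives d only for two independent groups compared on a single measure. It does not do so for a three-group by two-time interaction. A reader will set .33 beside the pilot's .89 as if both were on one scale, and conclude that 90 completers can find a small difference between active treatments.

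If that is wrong, the document overstates what the trial can see, including at the reduced sizes in 11.4.7, to which the team would turn if recruitment were slow. It also makes a null result look more informative than it is, next to a sentence in 11.2 that attaches clinical meaning to non-inferiority.

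**Working it through.** **Inputs.** From 11.4.4: N = 90 (30 per arm), k = 3 groups, m = 2 measurements, alpha .05, power .80, nonsphericity correction 1. From 11.4.6: alpha .005. From 11.4.7: N = 75 and N = 45. Assumed: pre-post correlation ρ = .5, the value that reproduces the stated figures.

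**Step 1: reproduce the protocol's figures.** For the within-between interaction, λ = f²·N·m/(1−ρ), with df₁ = (k−1)(m−1) = 2 and df₂ = (N−k)(m−1) = 87 for N = 90. Solving for 80% power at ρ = .5:

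| Case | f | 2f | Protocol's d |
|---|---|---|---|
| N = 90, α .05 | .1665 | .333 | .33 / .335 |
| N = 90, α .005 | .215 | .430 | .43 |
| N = 75, α .05 | .183 | .366 | .37 |
| N = 45, α .05 | .240 | .480 | .48 |

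All four match. With f = .335/2, power at N = 90 is 80.5%. Other correlations do not match at N = 90: 2f is .47 at ρ = 0, .39 at ρ = .3 and .26 at ρ = .7. Entering .335 directly as f would need only N = 25. A one-way ANOVA of change scores on 90 participants also gives f = .333, so the two routes cannot be told apart. On either route the number is not a difference between two arms in SD units.

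**Step 2: what f = .1665 means between arms.** At ρ = .5 the SD of change is σ√(2(1−.5)) = σ, so SD of change and raw-score SD coincide. The f of the change scores is 2 × .1665 = .333.
- One arm apart from two equal arms: .333 × 3/√2 = 0.71 SD.
- Three evenly spaced arms: .333 × √6 = 0.82 SD.

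**Step 3: the pairwise contrasts.** Aim 3 compares FA and OM each with MBCT. Two-sided noncentral t, noncentrality d√(n/2), 80% power:

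| Case | Detectable difference (SD) | Power at the protocol's d |
|---|---|---|
| 30 per arm, α .05 | 0.74 | 24% (at .33) |
| 30 per arm, α .005 | 0.98 | 12% (at .43) |
| 25 per arm, α .05 | 0.81 | 25% (at .37) |
| 15 per arm, α .05 | 1.06 | 25% (at .48) |

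Eighty percent power at d = .335 needs about 141 per arm, or 3 × 141 = 423 completers.

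**Step 4: allow for a more efficient analysis.** Section 11.3.2 plans a multilevel model over several time points. Assume compound symmetry, a constant post-baseline effect, baseline adjustment and no clustering. With p post-baseline measures, the residual SD is √[(1+(p−1)ρ)/p − ρ²]. Multiply 0.736 by this for the detectable difference at 30 per arm:

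| Post-baseline measures | ρ | SD factor | Detectable (SD) | Power at .33 |
|---|---|---|---|---|
| 1 | .5 | .866 | 0.64 | 31% |
| 1 | .7 | .714 | 0.53 | 42% |
| 2 | .5 | .707 | 0.52 | 43% |
| 2 | .7 | .600 | 0.44 | 55% |

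In a two-timepoint analysis, .33 SD becomes detectable only at ρ of about .9, where 2f would be .149 and the protocol's own figures would not reproduce.

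**Step 5: precision.** The 95% CI half-width at 30 per arm is t(.975, 58) × √(2/30) = 0.52 SD unadjusted, or 0.52 × .866 = 0.45 SD with baseline adjustment at ρ = .5.

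**The case against.** The strongest reply is that the computation is sound and only the label is wrong. By the usual convention for f, in which .25 is medium, values of .167 to .240 are fairly called small or approaching medium. That stands, and it is why relabelling as f is an acceptable remedy. It does not rescue the text as written, which calls the values d, places them after a pilot Cohen's d, and applies them to differences between treatments.

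Second, 24% describes an unadjusted two-timepoint comparison, not the planned multilevel model. This also stands. The adjusted and repeated-measures figures of 31–55% belong beside it, so 24% should not be presented as the trial's power. Clustering from group randomization is left out throughout, and any positive intragroup correlation would worsen all these figures.

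Third, the study is a pilot aimed at estimation, its size is bounded by capacity, and no significant clinical difference is expected. This lowers the consequence but does not make the power statements true.

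A reader might infer that the trial plans to claim non-inferiority and is underpowered for it. The protocol does not support that: 11.2 sets no margin, test or decision rule, and 11.4.1 leaves the definitive comparison to a larger trial. A margin built from the .89 pilot effect would be invented, and that effect comes from the BDI, which is not an endpoint here. Nor do the documents show that f was deliberately doubled and renamed.

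**Conclusion.** The point holds as a mislabelled effect size with a false detectability claim in 11.4.4, 11.4.6 and 11.4.7. On the protocol's own two-timepoint basis, 30 per arm detects about 0.74 SD between two arms, not .33, and power at .33 is about 24%. Under the more efficient analyses in the working, the detectable difference is about 0.44–0.64 SD and power about 31–55%. These figures assume correlations of .5 to .7, compound symmetry and no clustering; none reaches 80%.

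On 11.2 the point is narrower. With an unadjusted half-width of about 0.5 SD, a non-significant result would leave differences of that order open, so the non-inferiority sentence needs a limit on its reading. Because the trial is an estimation pilot and nothing in its design or conduct depends on the correction, this is a correction of statements rather than a flaw that blocks the trial.

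**What to change.** In 11.4.4, 11.4.6 and 11.4.7, either relabel the four values as Cohen's f for the interaction (.167, .215, .183, .240) or replace them with the pairwise differences (0.74, 0.98, 0.81, 1.06 SD; two-sided, two time points). In either case:
- state the assumed pre-post correlation of .5 and that clustering is ignored;
- remove the claim that a small d between arms is detectable;
- give power at d = .33 with 30 per arm as a range by analysis: about 24% unadjusted, about 30–55% with baseline adjustment or repeated measures, with the assumptions named;
- state the expected 95% CI half-width, about 0.5 SD unadjusted.

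In 11.2, add that a non-significant difference will not be read as non-inferiority, and that the FA–MBCT and OM–MBCT differences will be reported with 95% CIs.

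The cost is wording only. Enrolment, endpoints and analysis stay as they are; the stated sensitivity becomes less favourable.

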**Output**

**Total sample size = 90**  
**Effect size d = .335**

### 11.4.5 Additional Sample size considerations +modifications

#### 11.4.5.1 Attrition

Based on pilot studies, we estimated 15% attrition rate (Shahar et al., in press) so that we need to enroll a total of 105 subjects (35 per group) in order to have 90 completers.

#### 11.4.5.2 Sample size adjustment due to group randomization

Group randomization may require an increase in sample size to maintain power, if the responses of subjects in same group are correlated (intragroup correlation). However, if intra- group correlation = 0, then there is no need for adjustment (Friedman et al., 2010)

In a set of MBCT RCTs that used group randomization procedures and multilevel modeling analysis, Williams (2008) estimated IGCs for depression related outcomes (BDI, relapse rate). Most IGCs were slightly negative, were all smaller than .01 and none of the IGCs were significantly different than 0. Furthermore, a comparison of results corrected vs uncorrected for IGC yielded no difference. Thus, group randomization does not contribute to inflated IGC because the participants in each cohort are selected at random and do not share any common characteristic. Furthermore, sharing the same treatment group experience does not appear to have any effect on outcome either.

Based on this data, we do not plan on adjusting the sample size because of group randomization. We will check the IGC during preliminary analysis, and add into the model if it greater than 0.

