**Timeline overview of the entire award (years 1-5)**

Preparation for this study will start in year 1-2, including treatment module development/refinement, training in assessments and participant recruitment. The original grant timeline allocated a minimum of 3.5 years (42 months) and a maximum of 4 years (48 months) to complete the treatment and data collection portion of the K-award. If the first treatment begins in the spring of 2013, then data collection is scheduled to be complete in Aug 2016 (42 months) or Dec 2016 (48 months).

The total target recruitment is 105 enrolled/90 completers. The number of groups and number of participants per group will depend on recruitment rates, but is estimated to be 9-12 groups of 8-12 enrolled (7-10 completer) participants. Each “group” requires a four month block of time that contains pre and post assessments and 2 months of treatment.

Thus, the plan for the next 3 cycles would be to run one group in the spring 2013, one in the summer 2013 and one in the fall of 2013. The number of completers for the first (spring 2013) group will be known by June 1st 2013.

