### **7.1.4.3 Group Randomization**

Treatment randomization is performed at the group level, rather than the individual level. For example, each group of 4-16 participants will be randomly allocated into one of three treatments (i.e. group randomization) 9 different times.

**Stratification:** Stratification by baseline characteristic will not be used because it would delay treatment, and because it is not possible in group randomization designs. Group differences in baseline characteristics will be assessed (see [Preliminary Analyses section](#))

and if present, incorporated into analysis plan under the guidance of statistical mentors. Seasonal effects will be accounted for by balancing treatment equally over the 3 seasons (spring, Summer, fall).

**Masking:** The results of each treatment randomization will be recorded and communicated by an independent RA that is not involved in patient contact.

**Procedure:** An independent statistician, [name] PhD., at Brown Center for Statistical Sciences is responsible for generating random treatment randomization sequences. The results of each randomization will be recorded by the statistician and communicated to the PI who is one of the co-therapists for each treatment. The PI will maintain the treatment location information in a password-protected electronic file, and provide de-identified codes to signify different treatments during analysis.

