## 11.3 Analysis Plan:

### 11.3.1 Preliminary Analyses:

The purpose of the preliminary analysis is to investigate the data for patterns that may impact subsequent analyses, such as: group differences at baseline, differential attrition, compliance or instructor qualities, competence, adherence or ratings. Because we used a group randomization, we must also assess the degree to which group-ness influences outcome (i.e. intra-group correlation).

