### 11.3.2 Primary Analyses:

**To asses and compare the effects of FA and OM modules on clinical efficacy vs standard MBCT** Multilevel Modeling (MLM) will be used to compare the trajectories of clinical improvements in affective states (IDS, DASS PANAS, WBS) for each treatment.

Level 1 variables will include depression, negative affect and wellbeing scores at multiple time points.

Level 2 variables will include treatment type, meditation practice amount and demographic variables (age, sex, education). A MLM approach (Bryk & Raudenbush, 1992) was chosen for analysis because it is well suited to repeated measures designs, yields more information than ANOVAs (i.e. allows for individual growth curves), has the ability to retain missing cases, and fits my training goals of advanced statistical analysis skills for treatment research.

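### Whole groups are randomised, but the group effect enters the model only if its estimated correlation exceeds 0, which 9 to 12 groups cannot decide; fit the group always

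*Protocol*

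**What the plan says.** Section 7.1.4.3 fixes the unit of allocation: "Treatment randomization is performed at the group level, rather than the individual level". It adds that "each group of 4-16 participants will be randomly allocated into one of three treatments (i.e. group randomization) 9 different times". The timeline in section 5.2 gives the number of groups as "estimated to be 9-12 groups of 8-12 enrolled (7-10 completer) participants".

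Section 11.3.2 describes the primary multilevel model with two levels. At the lower, "Level 1 variables will include depression, negative affect and wellbeing scores at multiple time points". At the upper, "Level 2 variables will include treatment type, meditation practice amount and demographic variables (age, sex, education". No level for the treatment group is named, and treatment, which is assigned to groups, is entered at the participant level.

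Section 11.3.1 says the influence of the group on outcome has to be assessed, as a preliminary step. Section 11.4.5.2 says what follows from that assessment: "We will check the IGC during preliminary analysis, and add into the model if it greater than 0". It declines to adjust the sample size, citing earlier MBCT trials with correlations below .01 and not significantly different from 0. It reasons that "the participants in each cohort are selected at random and do not share any common characteristic". Section 11.4.4 computes power for 90 independent participants.

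**The concern.** Treatment is an exposure of the group, so an arm comparison has to be judged against variation between groups within arms. The stated rule lets the data decide whether that variation is in the model. The data for the decision are 6 between-group degrees of freedom with 9 groups, or 9 with 12.

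If a non-positive estimate often occurs when the true correlation is above 0, the rule removes the randomised unit in just those trials where chance made the between-group variation look small. Intervals are then too narrow. The trial's product is effect estimates for a larger trial, and section 11.2 gives clinical meaning to non-inferiority. Both depend on interval width.

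The supporting reason is also too strong. Members of a cohort share a class, a recruitment wave and possibly a second therapist.

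**Working it through.** **1. The plan's own figure.** Inputs from 11.4.4: 3 arms, 2 measurements, N=90, alpha .05, d=.335. The correlation between measurements is not given. I assume .5, because it reproduces the stated figures. With f = d/2,

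lambda = f² × N × 2 / (1 − .5) = (.1675)² × 360 = 10.10, on 2 and 90 − 3 = 87 df.

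The critical F is 3.10 and power is .805. The stated N is therefore right for individually randomised participants.

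**2. How often the rule drops the group.** Take change scores, 9 groups of 10, total variance 1. The between-group mean square has 9 − 3 = 6 df and the within-group mean square has 90 − 9 = 81 df. The estimated correlation is at or below 0 when the first does not exceed the second:

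P(drop) = P( F(6, 81) ≤ (1 − IGC) / (1 + 9 × IGC) ).

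At IGC .05 the bound is .95/1.45 = .655, which gives .31. At .01 it is .99/1.09 = .908, which gives .51.

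**3. What follows.** Simulation of a pairwise arm contrast, 2 million draws per row. *Dropped* means tested on 87 df without the group. The last two columns cover both branches, with the group tested on 6 df or by Wald z when it is added.

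| True IGC (assumed) | P(drop) | SE used / true SE, dropped | Size, dropped | Overall, 6 df | Overall, Wald z |
|---|---|---|---|---|---|
| 0 | 57% | 1.00 | 5.0% | 3.1% | 3.9% |
| .01 | 51% | .955 | 6.1% | 3.5% | 4.5% |
| .02 | 45% | .915 | 7.3% | 3.8% | 5.1% |
| .05 | 31% | .82 | 10.9% | 4.4% | 6.5% |
| .10 | 17% | .70 | 17.0% | 4.9% | 8.0% |

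Fitting the group always, on 6 df, gives 5.0% in every row. With 12 groups of 7.5, P(drop) is 55%, 50%, 44%, 31% and 16%, so more groups within the planned range do not rescue the decision.

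**4. The detectable effect with the group always fitted.** The error df are 6 (9 groups) or 9 (12 groups), and the critical F rises from 3.10 to 5.14 or 4.26. At IGC 0 and lambda 10.10, power is .58 or .67. The d detectable with 80% power is .43 or .39. At IGC .05 with 9 groups, lambda is 10.10/1.45 = 6.97, power is .43 and the detectable d is .52. No season term is included here.

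**The case against.** The strongest reply is that the protocol's own evidence puts the correlation below .01. At .01 the standard error in the dropped branch is 3 to 5% too small (12 and 9 groups), and overall size under the literal rule is below 5%. Sections 11.1 and 11.4.1 aim at estimates rather than significance levels, and 11.3.1 already commits to assessing the group effect. All of this stands, and it lowers the grade. It does not make a non-positive estimate from 6 df a sound reason to remove the randomised unit. The cited correlations also concern the BDI and relapse, whereas the models cover IDS, DASS, PANAS, WBS and laboratory measures.

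Three stronger readings do not hold.

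- **That standard errors and df are wrong throughout.** At a true IGC of 0 the 87-df test keeps its 5%. The protocol sets no df method for the mixed model, and that choice may be left to an analysis plan.
- **That type I error is 10.5% or 16%** (IGC .05 and .10). Those figures describe always ignoring the group, which the protocol does not propose.
- **That season inflates the error.** Section 7.1.4.3 balances treatments over the three seasons, so a season effect common to the arms cancels from arm contrasts. With an assumed season-only variance of .05, the test ignoring groups had size 4.6 to 4.7%. A 6-df test without a season term fell to 2.6 to 2.7%, and adding season (4 df) restored 5%.

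Therapists are only partly a cohort-specific factor, since the investigator co-leads every treatment.

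**Conclusion.** The conditional rule in 11.4.5.2 is a poor one and should go, as a should-fix. Its harm is confined to trials where the group is dropped and the true correlation is above 0. The error there is small at the cited correlation (size about 6% at .01) and material only at assumed values of .05 to .10 (about 11% and 17%). Over both branches, size is about 3 to 5% with group df, or up to 8% at IGC .10 with Wald z.

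The consequence that does not depend on a positive correlation is precision. An analysis that respects the 9 or 12 randomised units has power of about .58 or .67 at d=.335, not .80. These figures assume equal group sizes, a correlation of .5 between measurements and no season term.

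**What to change.** - In 11.4.5.2, delete the rule that makes the group effect depend on its estimate.
- In 11.3.2 and 11.3.3.1, fit treatment group as a random effect, nested in arm, in every arm comparison whatever its estimate. Base the df on the number of groups: 6 with 9 groups, 9 with 12.
- If allocation is balanced over seasons, include season as a term. This leaves 9 − 1 − 2 − 2 = 4 df with 9 groups.
- Remove the claim that cohort members have nothing in common.
- Beside the participant-level detectable effect in 11.4.4, state the one on group df: d of about .43 (9 groups) or .39 (12 groups) at IGC 0, with the assumed correlation between measurements.

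The change needs no further participants or data. The price is wider intervals: the critical t is 2.45 on 6 df against about 1.99 on 87, a factor of 2.45/1.99 = 1.23 at the same standard error. With season fitted on 4 df it is 2.78.
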